### 4.3 BLINDING

Due to the characteristics of the study design where the dietetic guidance of the study subjects is the inherent intervention in the study, any blinding of the dietician or subjects is not possible. Each dietician will be responsible for guidance of subjects in all five dietary intervention groups.

By any analyses of data obtained prior to study termination, it will be assured that these analyses will not influence the ongoing study and hence the final outcome of the study.

These restrictions will be inferred to exclude any bias introduced by the study personnel.

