## 4.2 METHOD OF ASSIGNING FAMILIES TO DIETARY GROUPS

The eligible families will be allocated to a dietary intervention group using a simple block randomization procedure with centre, number of obese parents in the family and BMI (greater or less than 34, screening value) as stratification criteria by a third party with no knowledge of the

subjects that may affect the outcome of the study. Approx. 11 families are randomized to each of the 5 dietary intervention groups. The outcome in the dietary intervention groups will be compared to each other and to the control group.

Approx. 6 subjects in each dietary group (3 men and 3 women) will be randomized to **Subgroup a** (7-day food record, BMR and DLW measurements, physical activity using pedometers, meal test). Approx. 7-10 subjects in each dietary group will be randomized to **Subgroup b** (extra fat biopsy day 3 into LCD diet).

Participation by (adult) subjects in the sub-groups is entirely voluntary and separate information sheets and consent forms will be signed.

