### **7.2.3 BODY COMPOSITION**

Body composition will be determined for adults and overweight children 4 times during the study, on CID 1-4, by DEXA or bioimpedance

A DEXA scanner (Lunar Radiation Co., Madison, Wisconsin, USA) will be used to determine lean tissue mass (LTM), fat mass (FM), bone mineral content (BMC) and total body weight (TBW). All scans will be performed using the appropriate scan velocity, depending on body weight and sagittal height. The expected scan time is 5-10 min. The subjects will receive 0.04 – 0.08 mrem of radiation pr. scan.

All subjects will be scanned in a fasting condition and only wearing light clothing. The total scan area will measure 61 cm x 196 cm. For subjects exceeding the grid, DEXA scans will be performed by excluding the outermost part of the arm and/or the thigh.

The subjects will be wrapped in a broad belt, made of coarse tightly woven cloth and closed using Velcro straps to maintain their position during the scan.

The same (or similarly competent) scan-operator will be used throughout the study.

The same scan-analyzer will be used throughout the study, to avoid variation in analysis of the scan results. Quality control and calibration check using the Lunar Aluminum Spine Phantom (LSP) will be performed at least once a week.

DEXA subject information will be handed to the subjects.

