### 8.2.2 MAIN OUTCOME MEASURES

The main outcome measures in this study for adults are body weight loss maintained (kg), changes in body composition (DEXA/bioimpedance), proportion of subjects maintaining > 0, 5 and 10% of initial weight loss, and drop-out rate. Main outcome measures for children are changes in the proportion of overweight and obese children at 6 and 12 mo, and changes in age-associated BMI, % whole body fat and drop-out rate.

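### Section 4.3 says personnel bias is excluded, but its measures do not concern outcome assessment, and no masking is provided for analysing the DEXA scans behind a main outcome

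*Protocol*

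**What the plan says.** Section 4.3 gives the reason for an open design: the dietetic guidance is itself the intervention, so "any blinding of the dietician or subjects is not possible". It then lists two measures. The first is "Each dietician will be responsible for guidance of subjects in all five dietary intervention groups". The second concerns any analysis of data before the study ends: "it will be assured that these analyses will not influence the ongoing study". The section closes with "These restrictions will be inferred to exclude any bias introduced by the study personnel".

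Section 7.2.3 describes body composition, measured by DEXA or bioimpedance at CID 1 to 4. On the reading of DEXA scans it says "The same scan-analyzer will be used throughout the study, to avoid variation in analysis of the scan results".

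Section 8.2.2 lists "changes in body composition (DEXA/bioimpedance") among the main outcome measures for adults, and percentage whole body fat among those for children.

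**The concern.** The closing sentence of 4.3 claims a property of the whole trial: that study personnel introduce no bias. A reader of the protocol, or of a paper that relies on it, would take this to cover the staff who measure and read the outcomes. The section contains nothing that does so.

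One person analysing every scan removes differences between readers. It does not protect against a reader who knows the diet group, because any tendency linked to that knowledge would then run through all the scans. At stake is the credibility of the DEXA part of a main outcome in a trial where subjects and dieticians are necessarily open. Masking the reading is one of the few protections still available in such a design.

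**Working it through.** There is no figure to reproduce and no arithmetic that the documents could feed. The check sets each safeguard in the protocol against the source of bias it can act on, and then asks whether any of them reaches outcome assessment.

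1. **Dieticians across all five groups (4.3).** This prevents a difference between dieticians from being confused with a difference between diets. It acts on delivery of the intervention.
2. **Early analyses must not influence the study (4.3).** This acts on feedback from accumulating data to conduct. It does not act on how a measurement is taken or read.
3. **Third-party randomisation (4.2).** The allocation is made "by a third party with no knowledge of the" subjects that could affect the outcome. This protects allocation and has no effect on later measurement.
4. **One scan-analyzer (7.2.3).** The stated purpose is to limit variation in the analysis. That is consistency between readings, not masking.
5. **Other places where masking might appear.** Section 7.2.1 (weighing), the rest of 7.2.3 (scan operator, calibration), the visit list in 7.1 and Section 8.2 (statistical procedures) contain no masking provision.

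So no safeguard in the protocol reaches outcome assessment, and the closing sentence of 4.3 claims more than the listed measures can deliver.

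**Is the stated obstacle relevant to the scan reader?** The reason in 4.3 is that guidance to subjects is the intervention. That binds the person who gives the guidance and the person who receives it. Someone analysing a stored scan does neither, so the reason does not prevent masked reading.

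**Which readings are exposed?**
- *Adults.* The visit list puts randomisation at visit 8 (7.1.1.6) and describes CID 2 at visit 9 as following it (7.1.1.7). Section 8.2.4 uses CID 2 as the covariate and compares groups at weeks 26 and 52 (CID 3 and CID 4). By the visit list, the covariate scan and both outcome scans are therefore all taken after allocation. Section 3 mentions CID 2 before it mentions randomisation but states no order. If CID 2 came first, the two outcome scans would still be exposed.
- *Children.* The covariate is CID 1, taken before randomisation, so only the later scans are exposed. The visit lists limit body composition to overweight children aged over 12, again by DEXA or bioimpedance.

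**What a reading bias would do.** Let a reader's group-related tendency be d_b in the covariate scan and d_f in the follow-up scan, with covariance-analysis slope b. The adjusted group difference then shifts by d_f − b·d_b. A constant tendency partly cancels for adults, but the shift is zero only if d_f = b·d_b. For children, whose covariate precedes allocation, d_b = 0 and the whole of d_f remains. The documents give no value for d_b, d_f or b, so no size follows.

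**The case against.** The case against has real weight, and several stronger readings that a reader might infer do not stand.

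- **That 4.3 restricts only early analyses.** It also has each dietician serve every group, which is a genuine measure. It does not touch outcome assessment, so the conclusion is unchanged.
- **That the analyst is unmasked or knows the diet group.** The protocol does not say so. It names only dieticians and subjects as impossible to blind and is silent on the scan reader. The supportable statement is that no masking is provided for. Taking scan-analyzer to mean a person is natural beside the scan-operator named in the same section, but it is not explicit.
- **That the analyst chooses which tissue to leave out in large subjects.** Section 7.2.3 says "For subjects exceeding the grid, DEXA scans will be performed by excluding the outermost part of the arm and/or the thigh". As worded, this happens when the scan is performed, with the subject present, so it points to the operator. Coding stored scans would not address it, and it is not evidence of judgement at the reading step.
- **That the powered comparison is threatened.** Section 8.2.7 names weight change to week 26 as the primary efficacy parameter. Weight comes from a calibrated scale (7.2.1), and DEXA reading cannot shift it. Setting an assumed error in fat mass against the 1.0 kg of 8.2.7 would compare two different outcomes, with no support in the documents for the assumed error.
- **That the protocol expects high protein and low GI to win.** Section 9.3 says only what success could support, the background calls the GI literature conflicting, and the hypotheses in 8.2.5 are two-sided.
- **That laboratory handling is also at fault.** Nothing in the protocol shows a defect there.

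What stands of the objection is that the point is narrow. What it does not answer is that the closing sentence of 4.3 is a positive statement the design cannot support, and that a workable safeguard on a main outcome is not provided.

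**Conclusion.** The point holds in limited form. The last sentence of 4.3 is wrong as a description of the design, because the measures it refers to do not concern outcome assessment. Separately, the protocol provides no masking for the analysis of DEXA scans, although these feed a main outcome and nothing in the stated reason for open treatment prevents it.

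The scope is DEXA readings in adults and in the older overweight children who are scanned. Bioimpedance readings and scale weight lie outside it. No magnitude can be derived, and the documents do not show that any bias would occur or in which direction. The conclusion assumes that the scan-analyzer is a person and that stored scans can be read without the subject present. Inclusion of the adult covariate scan also assumes that the visit list gives the true order of randomisation and CID 2.

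Masking of outcome assessors belongs in the protocol, and 4.3 already makes a claim on the matter, so this is not a detail that can be left to a statistical analysis plan. It is a cheap improvement together with a correction of wording, not a flaw that undermines the trial.

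**What to change.** Two changes of text:

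1. **Section 7.2.3.** State that the existing scan-analyzer analyses all DEXA scans under a code, masked to diet group.
2. **Section 4.3.** Replace the last sentence with an accurate one: subjects, dieticians and on-site measurements are open; DEXA scans are analysed masked to diet group; bias from study personnel is reduced by these measures, not excluded.

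The cost is a small amount of work to code scan labels and keep the key away from the analyst. It needs no extra staff, visit or procedure and does not alter the diets. Masked reading does not cover how the scan is acquired, which is why the new sentence in 4.3 should say plainly that on-site measurement remains open.

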## 5. SUBJECTS

An estimated 75 families will undergo screening. Thus it is aimed to enrol a total of about 50 families in the dietary intervention study, allowing for drop-out.

### 5.1 INCLUSION CRITERIA

The inclusion criteria for the families are as follows:

- Families where both parents are < 65 years old, and where minimum one adult parent is obese (BMI>30) and the other parent is BMI>28.
- Families with 1-3 children, where at least one child aged between 5 and 18 years is overweight (defined according to Cole *et al.* (2), i.e. with an iso-BMI>25).
- Single-parent families with one obese (BMI>30) parent and minimum 1 overweight child aged between 5 and 18 years. Any other adult family members (including offspring) are excluded from the study. Children above the age of 16 may be excluded if they so wish.
- Healthy and no regular medication (exception oral contraceptives)
- All ethnic groups are allowed inclusion
- Smoking is allowed, provided subjects do not intend to change their smoking behaviour.
- All subjects should have an overall physical and psychological condition that the investigator believes is in accordance with the overall aim of the study.

### 5.2 EXCLUSION CRITERIA

The exclusion criteria for the adults are as follows:

---

 Children below the age of 5 are excluded and should continue to eat according to local dietary guidelines

*At enrolment:*

- Use of prescription medication marked with N
- Blood pressure above 160/100 mmHg (Subjects with SBP=159 and DBP=99 are allowed inclusion). Well regulated BP (<140/90 mmHg) using drugs is allowed if no change in BP and drug dose within last 3 months.
- Fasting blood glucose >6.1 mM at screening. Re-test is allowed.
- Known untreated hypercholesterolemia (>7 mM). Subjects using drugs for hypercholesterolemia are excluded.
- Known untreated hypertriglyceridemia (>3 mM). Subjects using drugs for hypertriglyceridemia are excluded.
- Drug-treated thyroid diseases (well substituted hypothyroidism is allowed inclusion)
- food allergies
- special diets (e.g. vegetarian, Atkins) within 2 months prior to study start
- Food intolerance expected to interfere with the study
- Regularly drinking > 21 alcoholic units/week (men), or > 14 alcoholic units/week (women)
- Elite athletes and subjects planning to engage in elite sports (i.e. planning major changes in physical activity during the study).
- Blood donation within the past 3 months before entering the study.
- Weight change of > 3 kg within 2 months prior to Clinical Investigation Day
- Mental disorders
- Eating disorders
- Pregnant or lactating women, or women who are planning to become pregnant within the next 18 months.
- Surgically treated obesity
- Participation in other clinical studies within the last 3 months
- Alcohol or drug abuse (based on clinical judgment)
- Subjects who are unable to give informed consent.
- Subjects with systemic infections
- Subjects with endocrine disease
- Subjects with malabsorption
- Subjects who are unable to engage in a 8 week LCD period

*At randomisation:*

- Families in which both adults fail to lose min. 8% of initial body weight during LCD period

The exclusion criteria for the overweight children are as follows:

- special diets (e.g. vegetarian, Atkins) within 2 months prior to study start
- food intolerance expected to interfere with the study
- Regularly drinking > 21 alcoholic units/week (male), or > 14 alcoholic units/week (female)
- Blood donation within the past 3 months before entering the study.
- Subjects with systemic infections / chronic disease
- Use of chronic medication, except for conditions like hayfever

### **5.3 PROCEDURE FOR EXCLUSION/DISCONTINUATION DURING THE STUDY**

A subject will be removed from the study treatment based on their own decision or if the investigator finds it medically necessary.

If any child or adult refuses to follow dietary instruction after starting the intervention, the other family members will still be allowed to continue in the study. However, if refusal (by adult or overweight child) occurs before the start of the LCD diet, then the family will not be included in the study.

When a subject decides to discontinue participation in the study, he/she should always be contacted in order to, if possible, obtain information about the reason(s) for discontinuation. Whenever possible, the subjects should return for an unscheduled visit at the time of or soon after discontinuation.

The following procedures should be performed at an unscheduled visit:

- Date of discontinuation
- Reason for discontinuation
- Adverse events
- Recording of any new concomitant drug therapy or any changes to ongoing concomitant drug therapy since last visit, any pharmacological treatment established prior to entrance in this study will be maintained as long as ethically possible
- DEXA scan or bioimpedance (body fat mass, body lean mass)
- Body weight
- Blood pressure
- Waist/hip and sagittal measurements
- Blood sample
- Compliance Questionnaire

Subjects may also be withdrawn from the study because of severe protocol violations.

These subjects will not be included in the analysis and will permanently be dismissed from the study. Reasons for dismissal should be carefully recorded in the source data.

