## Subjects

Families where both parents are < 65 years old, and where at least one parent is obese (BMI>30 kg/m^2) and the other is overweight (BMI>28 kg/m^2) will be offered inclusion in the study with the aim of losing weight and maintaining the weight loss. Families will have 1-3 children, and at least one child aged between 5 and 18 years will be overweight (defined according to Cole *et al.* (2), i.e. with an iso-BMI>25). A total of 150 adult subjects plus children (75 families) will be screened and approximately 135 adults are expected to be included in the initial weight loss phase of the study, with the aim of having a total of 110 subjects for the subsequent randomization to the 5 dietary

arms. This number will provide an anticipated completion of more than 80 subjects at the 12-month visit.

Subjects will be recruited through the department's waiting list, local press or via referrals from local general practices or from other medical departments. Radio/television or newspaper advertising may also be employed if necessary. Eligible subjects will only be included after they have been informed about the study and signed informed consent forms (including children, see Section 11).

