#### **7.1.1.20 Early termination**

The registrations include (listed by priority):

- Date & reason for discontinuation
- Adverse events & concomitant medication
- Physical examination including BP (only if early termination is due to adverse event)
- Weight
- Body composition (DEXA-scanning/bioimpedance)
- Blood samples
- End of day/compliance Questionnaire
- RTD4 Questionnaires?
- Waist/hip and sagittal measurement
- Nutritional counselling

There will be a maximum volume of 110 ml blood taken on each CID day and max. 2g adipose tissue.

BIDR questionnaire

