### **7.8.2 PREGNANCY**

Subjects who become pregnant during the study will be excluded (but the rest of the family will be allowed to continue).

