### 8.2.4 STATISTICAL METHODS FOR THE PRIMARY OBJECTIVES

Analysis of Covariance (ANACOVA) will be used to compare the main outcome measures in the intervention groups at week 26 and week 52 using the data from CID2 (after weight-loss, adults) or CID1 (children) as covariate.

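### Section 5.3 does not separate stopping the diet from leaving the study, so no outcome is planned after the date of stopping, even where the family still attends

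*Protocol*

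**What the plan says.** Section 5.3 begins with the diet: "A subject will be removed from the study treatment based on their own decision or if the investigator finds it medically necessary". Its next paragraph covers a child or adult who refuses the dietary instruction after the intervention has begun, and says only that "the other family members will still be allowed to continue in the study". The procedures that follow have a different trigger: "When a subject decides to discontinue participation in the study, he/she should always be contacted". They consist of that contact and one visit: "Whenever possible, the subjects should return for an unscheduled visit at the time of or soon after discontinuation". The items for that visit include body weight and body composition.

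Section 7.1.1.20 (adults) starts with "Date & reason for discontinuation" and lists one exit assessment. Section 7.1.2.13 does the same for children. Its heading limits it to overweight children, although the date and reason are marked for all children. Section 7.8.2 has a similar pattern: "Subjects who become pregnant during the study will be excluded (but the rest of the family will be allowed to continue".

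The outcome times are fixed elsewhere. Section 8.2.1 names weeks 26, 52 and 104, and section 8.2.4 uses analysis of covariance "to compare the main outcome measures in the intervention groups at week 26 and week 52". Of the 110 adults to be randomised, the Synopsis says: "This number will provide an anticipated completion of more than 80 subjects at the 12-month visit".

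**The concern.** The trial asks which ad libitum diet best prevents weight regain, and nobody giving or following the diets is blinded. People who abandon a diet may well be those who are regaining, and stopping may depend on the diet assigned. Control families keep their habitual diet and get no advice on its composition (section 3), so they have less to refuse than groups 1 to 4. Free food ends at week 26, which makes stopping in period 2 plausible in the four diet groups.

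If the weight of someone who has stopped is not taken at weeks 26 and 52, the effect in everyone randomised can be estimated only through assumptions about unseen values. A statistical analysis plan cannot recover weights that were never collected, so the Protocol has to settle this. It is a different question from which subjects the primary analysis includes.

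**Working it through.** **Step 1: what is planned after a stop.**

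| Event | What the Protocol provides | Later outcome visit named? |
|---|---|---|
| Removed from the diet (5.3, opening) | No procedure of its own | No |
| Refuses the diet after the start (5.3) | The rest of the family continues; the refuser's status is not stated | No |
| Leaves the study (5.3) | Contact and, if possible, one exit visit | No |
| Early termination (7.1.1.20, 7.1.2.13) | One exit assessment | No |

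The family visits at week 26 (CID 3), week 52 (CID 4) and week 104 take place anyway. They appear in 7.1.1.15, 7.1.1.18 and 7.1.1.19 for adults, and in 7.1.2.9, 7.1.2.11 and 7.1.2.12 for children. Nothing limits them to people still on the diet, and nothing asks those who have stopped to come.

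**Step 2: which outcomes are affected.**

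| Time of stop | Week 26 | Week 52 | Week 104 |
|---|---|---|---|
| Before week 26 | not planned | not planned | not planned |
| Period 2 (weeks 26 to 52) | already measured | not planned | not planned |

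**Step 3: size, from the Protocol's own figures.** Inputs from the Synopsis (Subjects): 110 adults randomised, more than 80 completing 12 months.

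- Non-completers at week 52: at most 110 − 80 = 30.
- Share: 30/110 = 27.3%.

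Because more than 80 are expected to complete, 30 is an upper limit. It counts every reason for non-completion, including refusal of all contact. The Protocol does not split off those who stop the diet but could still be weighed, so the recoverable number lies between 0 and 30. No corresponding figure is given for week 26.

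**Step 4: when the loss biases the comparison.** Let p be the share of an arm with no outcome, and g the extra regain of those people over the arm's completers. The completers' mean differs from the mean of all randomised by −p × g. For arms A and B the contrast is off by −(pA·gA − pB·gB). This is zero when p and g are the same in both arms. Bias therefore needs drop-out or regain to differ by arm, and the Protocol gives neither quantity.

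**The case against.** The strongest reply is that this is an inference from silence. The exit-visit sentence is governed by leaving the study, where an exit visit is proper. Section 5.3 uses different words for the two events and never equates them. Later attendance is not forbidden, and the CID visits are described as family meetings. This stands: a reader might infer that outcomes are lost by rule, but no sentence says so. What remains is that 5.3 implies the refuser is out and plans nothing afterwards.

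A reader might also infer that neither the week-26 nor the week-52 outcome is ever collected. The Protocol does not support that for stops in period 2, which already have CID 3, and section 8.2.7 names weight change to week 26 as the primary efficacy parameter.

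Nor does every missing-data model rest on the weight at stopping. Section 8.2.4 names baseline carried forward, and adults are weighed at many visits between week 0 and week 48, so trajectories up to the stop are available. Differential drop-out is not hidden either. Drop-out rate is a main outcome (8.2.2), and time to withdrawal gets a log-rank test (8.2.5).

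It is tempting to turn 27% into kilograms. If leavers are assumed to regain 2 to 6 kg more than stayers, one arm's mean is off by 0.273 × 2 = 0.5 to 0.273 × 6 = 1.6 kg. A 10-point difference in drop-out shifts the contrast by 0.10 × 2 = 0.2 to 0.10 × 6 = 0.6 kg. Both inputs are pure assumptions, and the first result cancels when the arms are alike. The 27% also refers to week 52, whereas the 1.0 kg target in 8.2.7 is for week 26. These figures should not be quoted as the size of the problem.

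Finally, the family-visit argument fails where a whole family leaves, or where the only parent leaves and the children stop too.

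**Conclusion.** The point holds as a gap in planned data collection. Section 5.3 leaves stopping the diet and leaving the study undistinguished, and no passage schedules an outcome after the stop for someone who could still be weighed. At most 30 of 110 adults (27%) would lack a week-52 weight. How many of these could be recovered, and whether the between-diet contrast is biased, cannot be determined from the Protocol.

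The conclusion rests on reading 5.3 together with the early-termination lists as the complete plan for people who stop. If centres already invite them to CID 3 and CID 4, the defect is one of wording only. Even then the wording is worth correcting, because outcomes missed under it cannot be recovered later and the remedy is cheap. It also helps the drop-out outcome, which is unclear while the two events share one date.

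**What to change.** In 5.3, 7.1.1.20 and 7.1.2.13, define two events, *stopped assigned diet* and *withdrew consent to follow-up*, each with its own date and reason. Ask those who only stop the diet to attend the existing family visits for:

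- weight to the CID standard in 7.2.1 (and height in children) at weeks 26 and 52;
- weight at week 104.

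Keep the exit visit as an addition. In 7.1.2.13, cover normal-weight children too, because the proportion of overweight and obese children is a main outcome.

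In 8.2.4, state that these weights enter the intention-to-treat analysis. That section currently restricts the primary analysis to subjects who completed the study, which could leave the new weights out. No diet or clinical rule needs to change.

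The cost is Protocol and consent wording, plus a weighing at visits that already take place. Some subjects will decline, and the weights obtained will include time off the diet. They therefore describe the effect of being assigned a diet, not of adhering to it.
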